### Design

The study will be a pretest posttest independent measures design with a five level experiment consisting of a control group and a 2 × 2 design for type of feedback (intrinsic or KR) and presence of topic contingent KP feedback in the form of articulation guidance. See Figure 3 for an overview of the aims, variables, outcomes and measures employed in this experiment.

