## Proposed analysis

The assessments of speech production will be transcribed to an Excel spreadsheet. Statistical analysis will be performed using the Statistical Package for the Social Sciences (IBM SPSS Statistics 24).

The key question to be addressed in this research is: How does feedback type during speech therapy session influence children's production performance. As such, the key dependent variable under analysis will be PCC, phonological process percentage of occurrence and percentage accuracy of trials. Published data of PCC in children's development (e.g., Dodd et al., 2002) suggest that this variable to be normally distributed. As such we intend to perform a full-factorial regression analysis on PCC with feedback condition, number of trials completed, and child age (4, 5, or 6 years) and severity as predictor variables. The full-factorial nature of this analysis will allow us to determine how the effects of condition and trials completed independently predict PCC and the extent to which these factors interact in their effects on PCC between pretest and post-test. For example, we may find that with certain types of feedback, the number of trials completed has a much greater effect than with other types of feedback. Similarly, we may find that some feedback types have a greater effect on performance for younger or older children. These analyses will also be completed with phonological process percentage of occurance at pretest and post-test and percentage accuracy of trials as a dependant variables

We will also conduct a Generalized Linear Model Analysis assuming a binomial distribution for the number of correct trials post “intervention” within a total of *n* trials where *n* may differ between children. The analysis will control for pre “intervention” language skills, age, and gender. Marginal means will be compared for the five groups using a Bonferroni correction for multiple comparisons. This analysis could assist in distinguishing the effects of real-world simulation vs. verification feedback and the presence of articulation guidance.

Motivation to persevere could be considered a variable that mediates the impact of type of feedback. Consequently, we will also perform a one-way ANOVA to determine how feedback condition influences motivation as measured by the number of trials and the duration of game play.

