A G-Power power analysis suggested a total sample size of 150 in order to detect a moderate to large effect size (*f* = 0.32) with 5% significance and 80% power. Our recruitment plan of 30 participants in each of our 5 conditions is consistent with the G-Power analysis suggestion to avoid type II error.

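### No main-effect, interaction or planned contrast is named for the 2 × 2 feedback factors, and the sample-size statement does not say which comparison it powers

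*Protocol article*

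**What the plan says.** The Design section sets out "a control group and a 2 × 2 design for type of feedback (intrinsic or KR) and presence of topic contingent KP feedback". Anticipated results predicts that the two arms with intrinsic feedback will do best on speech production and will also be the most motivating. That is a prediction about two arms pooled against two.

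Proposed analysis names three kinds of analysis:

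- **PCC**, then process occurrence and trial accuracy: a regression with feedback condition, trials completed, age and severity as predictors. The full-factorial label refers to crossing condition with those other predictors, not intrinsic/KR with KP.
- **An additional binomial generalized linear model** for correct trials, in which "Marginal means will be compared for the five groups using a Bonferroni correction for multiple comparisons". The stated purpose is "distinguishing the effects of real-world simulation vs. verification feedback and the presence of articulation guidance".
- **Motivation** (number of trials, duration of play): a one-way ANOVA on feedback condition.

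The same section closes with the sample size: "A G-Power power analysis suggested a total sample size of 150" to detect f = 0.32 "with 5% significance and 80% power". It names no test, outcome or comparison.

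**The concern.** The scientific questions are whether intrinsic feedback beats KR and whether articulation guidance adds anything. A 2 × 2 answers each by using all four game arms, 60 children against 60. None of the stated analyses does this by name. The one analysis said to separate the factors compares five marginal means under a Bonferroni correction, and each cell pair then rests on 30 against 30 at a reduced level.

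Two things are at stake. The trial could show that some groups differ and still give a weak answer on either factor, although the data would support a sharper one. And a reader may take the 80% in the sample-size paragraph to cover the factor comparisons, when nothing in the text ties it to them.

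**Working it through.** **Inputs.** From Proposed analysis: N = 150, five arms of 30, f = 0.32, 5% significance, 80% power. Assumed here: two-sided tests, unit SD, equal variances, no dropout, no gain from covariates, error df 150 − 5 = 145. The documents give no SD, so differences are in SD units.

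**1. The plan's own figure.** For a five-group one-way F test, λ = N·f², with 4 and N − 5 df.

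- 80% power needs N = 122 (λ = 122 × 0.1024 = 12.5), or 125 in equal groups.
- At N = 150, λ = 150 × 0.1024 = 15.4 and power is 88.8%; 80% power corresponds to f = 0.287.
- So 150 is not reproduced by that test. A numerator of 7 df comes close (N = 148; 80.9% power at 150). It would fit an overall test of four condition dummies plus trials, age and severity, but the article states no such test.

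**2. Precision of each comparison.**

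- Cell pair, 30 v 30: SE = √(1/30 + 1/30) = 0.258 SD
- Main effect, 60 v 60: SE = √(1/60 + 1/60) = 0.183 SD
- Interaction (difference of differences): SE = √(4/30) = 0.365 SD

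Power is from the noncentral t with 145 df and noncentrality d/SE. The value d = 0.64 is 2f, the two-group equivalent of f = 0.32, used as an illustration. For the interaction row, d is the difference of differences.

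| Comparison | Level | Smallest d with 80% power | Power at d = 0.64 |
|---|---|---|---|
| Cell pair, ten pairs | 0.005 | 0.955 | 36% |
| Cell pair, four within-factor pairs | 0.0125 | 0.872 | 48% |
| Cell pair, uncorrected | 0.05 | 0.728 | 69% |
| Main effect | 0.05 | 0.515 | 94% |
| Main effect, four contrasts | 0.0125 | 0.616 | 83% |
| Interaction | 0.05 | 1.030 | 41% |
| Interaction, four contrasts | 0.0125 | 1.233 | 22% |

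The level 0.005 is 0.05/10 and 0.0125 is 0.05/4. The count of ten is the number of pairs among five means; the article does not state it.

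**3. What f = 0.32 implies if the factors are additive.** Let each factor add δ, and scale so that the SD of the five means equals 0.32.

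- Control equal to KR (0, 0, δ, δ, 2δ): SD of means = 0.748δ, so δ = 0.32/0.748 = 0.43. A neighbouring pair at 0.005 has 12% power. The main effect has 64% at 0.05 and 43% at 0.0125.
- Control one step lower (0, δ, 2δ, 2δ, 3δ): SD of means = 1.020δ, so δ = 0.32/1.020 = 0.31. A neighbouring pair at 0.005 has 5% power. The main effect has 40% at 0.05 and 21% at 0.0125.

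The pooled contrast is far more sensitive in both patterns, but it does not reach 80% in either.

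**The case against.** The case for the plan has several parts.

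- **The Bonferroni step belongs to an additional analysis.** It is attached to the binomial model, not to the PCC regression. SD-scale power figures only approximate what happens in that model. This stands.
- **The factors are not ignored.** Groups 1 v 2 and 3 v 4 (Table 4) are simple effects of intrinsic v KR; groups 1 v 3 and 2 v 4 are simple effects of KP. A reader might infer that the trial never tests its two factors. The text does not support that: pooled main effects and the interaction are what is missing.
- **The 80% is never assigned to these pairs.** A reader might infer that the power claim is false, or that 150 is a miscalculation. Neither follows. For a five-group F test 150 is more than enough, and because the test is not identified the mismatch with 122 is not a proven arithmetic error.
- **A one-way ANOVA is valid** for asking whether condition affects motivation. This also stands; it is simply less direct than a 2 × 2 for the motivation prediction in Anticipated results.
- **A five-level condition term allows factorial contrasts, and an article may leave contrast coding to an analysis plan.** This carries some weight. But the article does state how the groups will be compared and which comparison is meant to separate the factors, and that choice does not match the declared design or its predictions.

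**Conclusion.** The point holds as a mismatch between design and stated analysis. The plan declares a 2 × 2 plus control and predicts an advantage for the pooled intrinsic arms, but names no main-effect, interaction or planned contrast. Its sample size rests on an f = 0.32 test that it does not identify.

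The loss is material. The smallest difference detectable with 80% power is about 0.96 SD for a cell pair if all ten pairs are corrected, against 0.51 SD for a main effect at 5%, or 0.62 SD at 0.0125. The direction does not depend on the inferred count of ten: even uncorrected, a cell pair needs 0.73 SD. The sizes rest on the mean-scale assumptions listed in the check.

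Factorial contrasts improve the position without guaranteeing 80% power, and the interaction stays underpowered. This should be changed; it does not invalidate the trial.

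**What to change.** 1. In the PCC regression, the models for the other outcomes and the binomial model, prespecify intrinsic v KR, KP v no KP and their interaction within the four game arms. Add pooled game arms v control for outcomes that the controls also have.
2. Analyse trials completed and duration of play by a 2 × 2 ANOVA in the four game arms. Controls do not play, so these data form a 2 × 2 already.
3. Keep cell-pair comparisons as secondary, and state how many the Bonferroni correction covers.
4. Keep N = 150. Name the test, outcome and numerator df behind f = 0.32.
5. Restate power for the planned contrasts. Say openly that main-effect power is about 40–64% at 5% (21–43% at 0.0125) if f = 0.32 arises from the additive patterns above, and that the interaction has about 41% power at 5% for a 0.64 SD difference of differences.

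The cost is revised analysis wording and a restated power paragraph, with no extra children or data. The downside is that individual cell-pair tests become secondary.

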### Recruitment of participants

Potential participants will be identified from the Australian Catholic University Speech Pathology in Schools program in Melbourne. This program operates in several Catholic Education Primary Schools in Melbourne. Parents of clients of this service who are identified as having a phonological delay or disorder will be provided with an information sheet about the study. Parents who wish for their children to participate will be required to contact the staff of the study. Additional participants will be recruited through advertisement in kindergartens, day-care centers and playgroups.

Stratified random sampling based on severity of speech disorder and will be used to allocate children to experimental conditions. This process will ensure that each condition includes similar proportions of children with either a mild, moderate or severe phonological disorder. Due to the nature of the intervention, participants and therapists cannot be blinded to the experimental condition. However, pre- and post-test assessments of speech production will be carried out by a researcher/therapist blind to the assigned condition.

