## Anticipated results

With respect to research question 1, this study aims to investigate the effectiveness of four different types of feedback in improving speech sounds in young children while using a multimedia platform. Each of the three theoretical frameworks for learning discussed in the Background section predict that KR, the prevalent feedback in speech learning applications, will be the least effective because it does not contain information to assist learners in improving their speech production (Shute, 2008). The conversational framework for multimedia learning predicts that intrinsic feedback will be more effective than KR feedback because it is most likely to resemble real-world speech learning experiences which can be built upon (Laurillard, 2002). This framework predicts that the most effective feedback overall will be intrinsic combined with topic contingent KP because children will be able to elaborate and refine knowledge gleaned from real-world experiences with lessons learned during speech pathologist/learner dialogue (Laurillard, 2002). Within the context of novice-expert learning (Mason and Bruning, 2001; Moreno, 2004) children who are more responsive to therapy (influenced by factors such as age and severity of disorder) might benefit from KR combined with topic contingent KP, possibly because they could benefit from smaller amounts of more focused feedback. This combination is also prevalent in speech pathology practice.

With respect to research question 2, the prediction that the two conditions with intrinsic feedback will be the most effective in improving speech production is accompanied by the prediction that these two conditions will also be the most motivating because they will be situated in natural and social scenarios that could be more visually appealing, possibly more challenging (Mayer, 2014b) while offering greater autonomy and relevance (Ryan et al., 2006) and consequently should encourage more trials and longer gameplay. We also anticipate that other features of the respective feedback types will emerge from the analysis to suggest variables that will improve their effectiveness.

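### The motivation outcomes get a one-way ANOVA that leaves out the severity strata and age; it is valid, but adding both would be a nearly free gain in precision

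*Protocol article*

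**What the plan says.** **Motivation analysis.** Proposed analysis names a single method for motivation: "we will also perform a one-way ANOVA to determine how feedback condition influences motivation as measured by the number of trials and the duration of" a child's play. A one-way ANOVA has one factor and no covariate or stratum. Outcome measurement classes motivation as a secondary measure, with play time counted up to 20 minutes.

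**Allocation.** Recruitment of participants states: "Stratified random sampling based on severity of speech disorder and will be used to allocate children to experimental conditions". The stated purpose is that "each condition includes similar proportions of children with either a mild, moderate or severe phonological disorder".

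**Other models in the same section.** The PCC regression takes feedback condition and number of trials, together with "child age (4, 5, or 6 years) and severity as predictor variables". Of the binomial model for correct trials the article says: "The analysis will control for pre “intervention” language skills, age, and gender". So the PCC regression uses both severity and age, the binomial model uses age, and the motivation ANOVA uses neither.

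**What depends on it.** Anticipated results predicts, under research question 2, that the two intrinsic conditions will be the most motivating and will lead to more trials and longer play. The ANOVA is the only analysis aimed at that prediction. In the PCC regression the number of trials is a predictor, not an outcome.

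**The concern.** Stratifying by severity makes the arms alike on severity, so severity adds little to the variation between arm means. If the analysis ignores the strata, any variation in trials or play time that severity explains stays in the residual. The test then uses a larger error variance than actually affects the comparison, and its real type I error falls below the nominal 5%.

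Age works differently because it was not stratified. If it predicts the outcome, leaving it out costs precision but does not disturb the 5% level.

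What is at stake is power, and the width of any interval reported, for the comparison of feedback types on motivation. Both variables are known at baseline, so adjusting for them would not bias the comparison.

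**Working it through.** **Inputs from the article.** Five conditions of 30; f = 0.32; 5% significance; 80% power (Proposed analysis). The control does not play the game (Abstract), so number of trials and play time exist for four arms, N = 120.

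**Assumed input.** The combined correlation ρ of severity and age with the outcome is not in the article. A range of 0 to 0.5 is shown, and no value in it is preferred.

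**The article's own figure.** For a one-way ANOVA with k groups, power is P(F′ > F crit), where F′ is noncentral F with k − 1 and N − k df and λ = N·f².
- With k = 5 and N = 150, λ = 150 × 0.1024 = 15.36 and power is 88.8%.
- For 80% power this test needs N = 122, so the stated 150 is not reproduced. It errs on the safe side, and the point made here does not depend on it.

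**Planned motivation test.** With k = 4 and N = 120, λ = 120 × 0.1024 = 12.288 on 3 and 116 df. Power is 83.6%.

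**Adjusted test.** Severity takes 2 df and age as a linear term 1 df, so the residual df are 116 − 3 = 113. The residual SD is multiplied by √(1 − ρ²), and λ becomes 12.288/(1 − ρ²).

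| ρ (assumed) | residual SD multiplier | λ | adjusted power | change from 83.6% |
|---|---|---|---|---|
| 0 | 1.000 | 12.29 | 83.6% | under 0.1 point lower |
| 0.1 | 0.995 | 12.41 | 84.0% | +0.4 |
| 0.2 | 0.980 | 12.80 | 85.2% | +1.6 |
| 0.3 | 0.954 | 13.50 | 87.2% | +3.6 |
| 0.4 | 0.917 | 14.63 | 89.9% | +6.3 |
| 0.5 | 0.866 | 16.38 | 93.1% | +9.5 |

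Unrounded, the ρ = 0 comparison is 83.62% against 83.58%. Entering age as three categories uses one more df and changes nothing visible.

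**Smaller effect.** At an assumed f = 0.25, unadjusted power is 60.7%. Adjusted power is 60.6% at ρ = 0, and 65.2%, 69.1% and 74.5% at ρ = 0.3, 0.4 and 0.5.

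**Type I error of the planned test (severity only).** Let ρₛ be the correlation of severity alone with the outcome, and suppose severity is exactly balanced across arms. With no difference between arms, the between-arm sum of squares is σ²χ² on 3 df. The within-arm sum is σ² times a noncentral χ² on 116 df with noncentrality 120ρₛ²/(1 − ρₛ²). The usual 5% cut-off then rejects in about 4.3%, 3.5%, 2.5% and 1.5% of trials at ρₛ = 0.2, 0.3, 0.4 and 0.5. Simulations with three equal strata agree to within about 0.2 points, and the severity-adjusted model stays near 5%.

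**The case against.** The strongest reply is that the harm depends on a relation the article never states. The sentence closest to supporting it speaks of "children who are more responsive to therapy (influenced by factors such as age and severity of disorder"). That concerns improvement in speech, not willingness to keep playing, and the motivation prediction that follows mentions neither age nor severity. The outcomes may also leave covariates little to explain: play time is capped at 20 minutes, the activity is expected to last about 10, and trials are expected to fall between 80 and 100. These objections stand. They are why the gain is given as a range that starts at zero.

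A reader might infer several stronger things that the article does not support:
- **That the error term is too large and the p-values are conservative.** This holds only if severity predicts trials or play time, which nothing in the article establishes.
- **That omitting age also distorts the test's level.** Age was not a stratification factor, so omitting it can cost only precision.
- **That the motivation comparison is underpowered.** At f = 0.32 the unadjusted test already exceeds the 80% target. The article does not tie f = 0.32 to motivation in particular, and any loss matters mainly for smaller effects.
- **That the planned test is invalid.** In a randomised comparison it is unbiased, and where it departs from 5% here it errs on the safe side.

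The type I error figures also assume exact balance, whereas the article promises only similar proportions and gives no stratum sizes.

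It might finally be said that covariates for a secondary outcome belong in an analysis plan that is not shown. That does not remove the point, because the article does not leave the method open: it names an unadjusted test.

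**Conclusion.** The point holds as a recommendation to gain precision on a secondary outcome. The motivation analysis as written follows neither the stratified allocation nor the covariates of the PCC regression, and no reason is given. At f = 0.32 with four arms of 30, adjusting would raise power by between nothing and about 9.5 points as the combined correlation goes from 0 to 0.5. A gain of 5 points needs a correlation of about 0.36. The size rests on that unstated correlation, on applying f = 0.32 to the motivation outcomes, and on a linear model for outcomes that are partly capped. The direction does not depend on its exact value: adjustment costs practically nothing if the covariates are irrelevant and helps if they are not.

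**What to change.** For each motivation outcome (number of trials, duration of play), replace the one-way ANOVA with a linear model (ANCOVA). Its main effects should be feedback condition (the four game conditions), severity stratum (mild, moderate, severe) and age. Report adjusted condition means and differences from that model.

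The cost is one sentence in Proposed analysis and about 3 of 116 residual degrees of freedom. It needs no new data, children or staff, because severity and age are already recorded for allocation and for the PCC regression.

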## Anticipated results

With respect to research question 1, this study aims to investigate the effectiveness of four different types of feedback in improving speech sounds in young children while using a multimedia platform. Each of the three theoretical frameworks for learning discussed in the Background section predict that KR, the prevalent feedback in speech learning applications, will be the least effective because it does not contain information to assist learners in improving their speech production (Shute, 2008). The conversational framework for multimedia learning predicts that intrinsic feedback will be more effective than KR feedback because it is most likely to resemble real-world speech learning experiences which can be built upon (Laurillard, 2002). This framework predicts that the most effective feedback overall will be intrinsic combined with topic contingent KP because children will be able to elaborate and refine knowledge gleaned from real-world experiences with lessons learned during speech pathologist/learner dialogue (Laurillard, 2002). Within the context of novice-expert learning (Mason and Bruning, 2001; Moreno, 2004) children who are more responsive to therapy (influenced by factors such as age and severity of disorder) might benefit from KR combined with topic contingent KP, possibly because they could benefit from smaller amounts of more focused feedback. This combination is also prevalent in speech pathology practice.

With respect to research question 2, the prediction that the two conditions with intrinsic feedback will be the most effective in improving speech production is accompanied by the prediction that these two conditions will also be the most motivating because they will be situated in natural and social scenarios that could be more visually appealing, possibly more challenging (Mayer, 2014b) while offering greater autonomy and relevance (Ryan et al., 2006) and consequently should encourage more trials and longer gameplay. We also anticipate that other features of the respective feedback types will emerge from the analysis to suggest variables that will improve their effectiveness.

